### Participants

#### Nurse-midwives

The inclusion criterias for the nurse-midwives in the intervention and control groups are: they hold a three year diploma in nursing-midwifery education, and they work on a daily basis in Public Health Centres with basic emergency obstetric care. All participants will be required to sign a consent form.

#### Study population

The women who attend antenatal care in the Public Health Centres will be included consecutively. Their inclusion criteria are: pregnant women with a Hb of less than 11 g/dl in the first trimester of pregnancy and who are living with their husband or other family members. The pregnant women with severe anaemia (Hb less than 7 g/dl), would first be referred to a doctor, then she could be included, if she does not need to be hospitalized. Pregnant women over twelve weeks of gestation will be excluded. Regarding to the agreement of patient management in our country, the pregnant women who infected by HIV, malaria, or hookworm should get the medical treatment from the specialist doctor. Therefore, women who are infected by HIV, malaria or hookworm will also be excluded.

Based upon the number of participants needed, the nurse midwives will be asked to recruit eligible pregnant women with anaemia. All participants will be required to sign a consent form to agree to participate in the study.

### Intervention

#### Training of the Four Pillars Approach

This training will be given to the nurse-midwives in order to introduce the new concept of the Four Pillars Approach in managing pregnant women with anaemia, and training them how to implement this model in Public Health Centres with emergency obstetric care. Based on international literature and experts’ opinion, we will develop a training module for the Four Pillars Approach in managing pregnant women with anaemia. At the end of this training, the nurse-midwives will have the knowledge and skill to manage pregnant women with anaemia based on the Four Pillars Approach.

The training will last eight hours, and consist of two sessions. The first session will be held in-class, and the second session will take place in the skills laboratory of the Nursing School of the Universitas Gadjah Mada Yogyakarta. A specialist in obstetrics and gynaecology, a senior teacher and a senior nurse will take part as teachers during the in-class session. Different educational methods will be used, such as power point slides, video and role play. In the skills laboratory session, training participants will be divided into six groups; each group consisting of ten to eleven participants. Every group will be directed by one tutor and one “simulated patient” (a person who acts like a pregnant women with anaemia). Case scenario, drama, demonstration and role play will be used to capture a real-life situation. All participants will be assessed and are required to pass this. The tutor will observe the competency of each nurse-midwife, and give an assessment to each participant based on the observation check list. There are four items to be observed by the tutor: procedure of treatment, communication, professional behaviour, and data registration. Those items are scored by using a Likert scale 1 – 3. Score 1 will be given if the performance of the nurse-midwife is unsatisfactory, score 2 if the performance is reasonable but could still be improved upon, and score 3 if the performance of the nurse-midwife is excellent and complete according to the protocol. All the nurse-midwives are required to pass this assessment exam with a minimum score of 60%.

#### Training module and booklet

A training module will be given to every nurse-midwife involved in the training programme. The training module consists of general information about the training, training materials (such as: physiological changes during pregnancy, anaemia in pregnancy, laboratory testing, the concept of the Four Pillars Approach, and professional behaviour for the nurse-midwife), the Four Pillars Approach protocol, and samples of reporting and Case Report Forms (CRF).

The booklets will be given to all pregnant women with anaemia in the intervention group, in order to increase their knowledge on the prevention of anaemia in pregnancy. The booklet will be designed with text and pictures to improve understanding of the information. It will also include a check list table to monitor and record the intake of iron tablet supplements, folic acid and vitamins. The husband or family member will be asked to remind the pregnant woman to take the tablets and record this in the check list.

#### Parenting class

In the intervention group, the husband or other family member will be asked to attend the antenatal care visits together with the pregnant woman and to accompany the pregnant woman to two parenting classes. During the first parenting class, the trained nurse-midwives will explain the content of the booklet. In the second parenting class, the trained nurse-midwives will offer the opportunity to the pregnant women and her companion to share their experiences. The duration of each parenting class will be one hour.

### Data collection

#### Characteristics of pregnant women

The nurse-midwives will collect the data of patient’s individual characteristics (such as: age, parity, job, the distance to the Public Health Centre from the patient’s house, and the availability of health insurance), medical history (such as: obstetric history, family health history), data about the current pregnancy (such as: Hb, antenatal examination results, parenting class attendance); and documentation relating to the number of antenatal visits, the number of non participants and reasons why, and the number of drop outs and reasons why.

#### Outcome measures

##### *Primary outcome*

Hb level, and the number of antenatal care attendances and skilled birth attendance at delivery are the primary outcomes of this study.

The Hb level will be measured before the twelfth week of gestation (T0) and between week 35 and 37 of gestation in the third trimester (T1). The difference between T0 and T1 in the intervention group will be compared with the difference in the control group. The antenatal care attendance will be counted based on the documentation of the nurse-midwives at the end of pregnancy. Skilled birth attendance at delivery will be identified from the patient’s medical records in the Public Health Centre or hospital. All primary outcomes of the intervention group will be compared to those in the control group.

##### *Secondary outcome*

The barriers and facilitating factors of the implementation of the Four Pillars Approach, as well as nurse-midwives’ satisfaction with the approach are the secondary outcomes.

Focused group discussion will be conduct to investigate the barriers and facilitating factors. The trained nurse-midwives, and the nurse-midwives coordinators will be involved in the focused group discussion. The nurse-midwives’ satisfaction about the implementation of the Four Pillars Approach will be measured concerning the quality of health services, procedural clarity, and communication between the nurse-midwives and patients, by using the questionnaire of Langer A [26] with some modification to adapt it to the local situation.

### Analysis plan

#### Intervention model development

Studying relevant literature, consulting experts in this field and indepth interviews with the nurse-midwives will be conducted to evaluate the implementation of the current antenatal care standard and to investigate nurse-midwives experiences in managing pregnant women with anaemia in Public Health Centres. The result of those activities will be used as a knowledge base for designing the new model for managing pregnant women with anaemia in Public Health Centres.

#### Monitoring of the study

Firstly, we will invite nurse-midwives, the heads of Public Health Centres, and the coordinators of the family health programme from the Health District Offices in Yogyakarta Special Province, to attend a one day seminar. The aim of this seminar is to disseminate information, and to give the feed back, on the concept of the new model for the Four Pillars Approach in managing pregnant women with anaemia. Secondly, the revisions of the new model will be done when it is needed, based on the result of the seminar discussions. Thirdly, we will develop a team trainer for the Four Pillars Approach in managing pregnant women with anaemia, which will consist of one obstetric and gynaecologist, two maternity nurse specialists, and six senior nurses. Then, the team trainer will give a one day training course on the Four Pillars Approach in managing pregnant women with anaemia to the nurse-midwives. At the end of the training, the trainers will evaluate the nurse-midwives’ knowledge and skills to implement the Four Pillars Approach in managing pregnant women with anaemia. Finally, during the period of implementation of the Four Pillars Approach in Public Health Centres (data collection); the research team will periodically monitor and supervise this.

### Data analysis and model building

Double entry of data will be performed in Epidata [27]. Data will be transferred to SPSS and validated in SPSS (version 20) [28] where all statistical analysis will be conducted. Descriptive statistics will be used to describe the study population.

As the pregnant women are clustered within Health Care Centres, the intracluster dependence of the outcomes of the intervention will be assessed by calculating Intracluster Correlation Coefficients (ICC’s) [29].

A non zero ICC will lead to using random intercept generalized mixed models for analyzing the results of the Four Pillars Approach: a multilevel logistic model for binary outcomes (skilled birth attendance in birthing process) and a multilevel linear regression analysis for continous outcomes (Hb level). Count data (frequency of antenatal care visit) will be analyzed by multilevel linear regression analysis as an approximately normal distribution will be expected.

When the ICC equals zero logistic regression and a general linear model will be used to model the outcomes of the study.

The model will include intervention yes/no as well as patient characteristics as possible confounders. The baseline T0 Hb level will be entered when modelling the Hb level at T1. The results will be expressed as difference at T1 for Hb level, odds ratio for skilled birth attendance and difference in number of antenatal care visits with 95% confidence intervals. Statistical significance is established at p-value = 0.05. Explained variance (R-squared) for the linear model and the multilevel logistic counterpart thereof [29] will be reported as model fit statistic.

Analyses will be performed according to the intention-to-treat principle.

ATLAS.ti will be used to support the analysis of the qualitative data from the semi structured interviews on nurse-midwives’ perception of their experiences in managing pregnant women with anaemia, as well as the barriers and facilitating factors of the implementation of the Four Pillars Approach.

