### Power calculation

We need a total of 360 pregnant women with anaemia: (1) to detect a minimum difference of Hb = 0.5 g/dl between the intervention and control groups after assuming a standard deviation of 1.01, with α = 0.05, a power of 0.80, ICC of 0.10 and a dropout percentage of 20%; (2) to detect an increase of 20% points in skilled birth attendance in labour, with a baseline (control) percentage of 50% and an Intra Class Correlation Coefficient (ICC) of 0.10 with α = 0.05, power of 0.80 and a dropout of 20%; and (3) to detect a mean difference in antenatal attendances of one visit between the intervention and control groups with standard deviation 2.1, with α = 0.05 and power 0.80, ICC of 0.10 and a dropout of 20% [30]. The sample size of 360 pregnant women with anaemia will consists of 180 pregnant women from intervention and other 180 pregnant women from control groups. The period of recruitment will be limited to three months, and every Public Health Centre will recruit at least seven pregnant women with anaemia consecutively.

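### The trial's own ICC estimate decides whether centre stays in the primary analysis, and a zero ICC is left undefined; the effect is small unless zero is judged by a significance test

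*Protocol article*

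**What the plan says.** The Data analysis and model building section of the protocol article recognises that women are clustered within centres and says that "the intracluster dependence of the outcomes of the intervention will be assessed by calculating Intracluster Correlation Coefficients (ICC’s". The result then selects the model:

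- If there is clustering: "A non zero ICC will lead to using random intercept generalized mixed models for analyzing the results of the Four Pillars Approach". This means a logistic version for skilled birth attendance and a linear version for Hb and the visit count.
- If there is none: "When the ICC equals zero logistic regression and a general linear model will be used to model the outcomes of the study".

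Neither branch carries a threshold or a test, and neither names its degrees of freedom.

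The Power calculation section assumes the same ICC for all three primary outcomes. For Hb it reads "with α = 0.05, a power of 0.80, ICC of 0.10 and a dropout percentage of 20"%. The Setting section gives 24 centres per arm, 48 in all.

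**The concern.** The intervention is given to whole centres, so information about its effect comes from 48 units. That is a property of the design, and an ICC estimate of zero does not change it. The rule nevertheless lets the estimate remove centre from the analysis. Three things follow:

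- Where the rule applies, the reference distribution moves from centre-level to individual-level degrees of freedom.
- The choice is made from each outcome's own data, so the three primary outcomes may be reported from different classes of model.
- A zero could mean a variance estimate on its boundary, a value that rounds to zero, or a non-significant test. The wording does not settle which, and the error rate depends on it.

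At stake are the type I error and interval width of the primary results.

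**Working it through.** **Inputs.** From Power calculation: 360 women (180 per arm), ICC 0.10, α 0.05 (taken as two-sided), power 0.80, dropout 20%; Hb difference 0.5 with SD 1.01; skilled birth attendance 50% against 70%; one visit with SD 2.1. From Setting: 48 centres. Hence 360/48 = 7.5 women recruited per centre, and 7.5 × 0.8 = 6 evaluable.

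**Step 1: the plan's sample size.** The design effect is 1 + (6 − 1) × 0.10 = 1.5. Unadjusted sizes per arm are 65 (Hb), 93 (skilled birth attendance) and 70 (visits). Multiply by 1.5, divide by 0.8, round up and double:

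- Hb: 97.5/0.8, giving 122 per arm, 244 in total
- Visits: 105/0.8, giving 132 per arm, 264 in total
- Skilled birth attendance: 139.5/0.8, giving 175 per arm, 350 in total

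The largest is within 3% of the stated 360, so 48 centres of 6 evaluable women is a fair picture of the planned trial.

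**Step 2: how often the estimate is zero or negative.** With balanced centres this happens when the between-centre mean square does not exceed the within-centre one. Its probability is P(F ≤ 1/[1 + 6ρ/(1 − ρ)]), with F on 46 and 48 × 5 = 240 df. At ρ = 0.10 the bound is 1/1.667 = 0.60, giving 2.0%. At ρ = 0.05 it is 0.76, giving 13%. At ρ = 0.02 it is 0.89, giving 33%. With 7.5 women per centre the figure at ρ = 0.10 falls to 0.7%.

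**Step 3: degrees of freedom.** The single-level model has 48 × 6 − 2 = 286, and the centre level has 48 − 2 = 46. The critical t is 1.968 against 2.013, about 2% in interval width.

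**Step 4: overall type I error.** 200,000 simulated null trials per ICC, 24 centres per arm, 6 women each, continuous outcome. Outside the zero branch the mixed model is tested on 46 df.

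| True ICC | Estimate ≤ 0 | Error, literal rule | Error, random intercept always kept, 46 df | ICC not significant at 0.05 | Error, that reading |
|---|---|---|---|---|---|
| 0 | 52% | 4.2% | 3.9% | 95% | 4.8% |
| 0.01 | 42% | 4.3% | 4.1% | 92% | 5.3% |
| 0.02 | 33% | 4.6% | 4.4% | 87% | 5.7% |
| 0.05 | 13% | 5.0% | 4.9% | 65% | 6.3% |
| 0.10 | 2% | 5.0% | 5.0% | 26% | 5.9% |

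If zero means an estimate below 0.005 (rounding to 0.00), the rule applies in 37%, 16% and 2.6% of trials at ICC 0.02, 0.05 and 0.10. Overall error is 4.6%, 5.0% and 5.0%, so rounding is harmless.

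**Step 5: only the trials with an estimate at or below zero.**

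| True ICC | Single-level SE / true SE | Error, plan | Error, random intercept on 46 df | Error, centre-level summary on 46 df |
|---|---|---|---|---|
| 0.02 | 0.95 | 6.3% | 5.7% | 7.6% |
| 0.05 | 0.89 | 8.3% | 7.5% | 9.4% |
| 0.10 | 0.80 | 11.8% | 11.1% | 12.7% |

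The last row rests on about 0.02 × 200,000 = 4,000 trials, so its Monte Carlo standard error is about √(0.118 × 0.882/4,000) = 0.5 percentage points.

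**The case against.** The strongest reply is that the rule does almost no harm as written. Any non-zero estimate keeps the mixed model, no significance test is mentioned, and on that reading overall error never exceeds 5%. At the planning ICC the zero branch is reached in about 2% of trials. How a zero is judged is also a detail that a condensed article may leave to the full plan. All of this stands, and it is why the point is minor.

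Three stronger readings are tempting, and none is supported.

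- *A reader might infer that dropping the cluster term is what makes the standard error too small.* In the zero-branch trials it is too small whenever the true ICC is above zero. But a random-intercept linear model with its variance estimated at zero returns the same standard error as the single-level model. A centre-level standard error in those trials is smaller still: 0.89, 0.84 and 0.77 of the true value at ICC 0.02, 0.05 and 0.10. The shortfall comes from selecting trials with little observed between-centre variation. With a true ICC of zero, the single-level standard error is correct.
- *A reader might set the error of 6% to 12% within the zero branch against the 5% that a centre-level test holds.* The first is a conditional rate and the second an overall one. Within the zero branch the alternatives also exceed 5% at these ICCs (Step 5).
- *A reader might say that a zero-ICC analysis contradicts the planning ICC of 0.10.* A planning ICC is a design value, not a forecast of every estimate.

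The objection leaves three things untouched: a switch driven by the data, the wrong degrees of freedom when it operates, and wording loose enough for a significance test to be read into it.

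**Conclusion.** The point holds in a limited form and is minor. An imprecise estimate decides whether the unit of allocation stays in the primary analysis, and the article does not say what counts as zero. Read literally, the cost is a critical t of 1.97 instead of 2.01 in the affected trials, with overall type I error at about 4.2% to 5.0%. Overall inflation, to about 5.7%, 6.3% and 5.9% at ICC 0.02, 0.05 and 0.10, appears only if zero is applied as a non-significant ICC. The text does not state that reading, but does not exclude it either.

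The figures assume balanced centres, 20% loss spread evenly, two-sided tests, a continuous outcome and no covariates. The multilevel logistic analysis of skilled birth attendance was not simulated. The centre is taken as the unit of allocation; that the two arms lie in different provinces is a separate matter.

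**What to change.** Delete the sentence that sends a zero ICC to single-level models. State instead that centre stays in the analysis of all three primary outcomes whatever the ICC estimate, with centre-based degrees of freedom (46 before covariates), and that the ICC is reported descriptively only.

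Do not add a rule that switches to a centre-level summary only when the variance is estimated at zero. That would be another data-driven switch, and in those trials it rejects more often than the present rule (Step 5).

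The cost is one sentence deleted and one added, with no extra data. The price is slightly conservative tests when the true ICC is near zero: about 3.9% to 4.4% overall at ICC 0 to 0.02. The change removes the switch and the wrong degrees of freedom. It does not bring the error back to 5% within the subset of trials whose estimate is zero.

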### Power calculation

We need a total of 360 pregnant women with anaemia: (1) to detect a minimum difference of Hb = 0.5 g/dl between the intervention and control groups after assuming a standard deviation of 1.01, with α = 0.05, a power of 0.80, ICC of 0.10 and a dropout percentage of 20%; (2) to detect an increase of 20% points in skilled birth attendance in labour, with a baseline (control) percentage of 50% and an Intra Class Correlation Coefficient (ICC) of 0.10 with α = 0.05, power of 0.80 and a dropout of 20%; and (3) to detect a mean difference in antenatal attendances of one visit between the intervention and control groups with standard deviation 2.1, with α = 0.05 and power 0.80, ICC of 0.10 and a dropout of 20% [30]. The sample size of 360 pregnant women with anaemia will consists of 180 pregnant women from intervention and other 180 pregnant women from control groups. The period of recruitment will be limited to three months, and every Public Health Centre will recruit at least seven pregnant women with anaemia consecutively.

## Discussion

The high prevalence of anaemia in pregnancy in Yogyakarta Special Province requires adequate nursing-midwifery care to prevent the adverse effects of anaemia in the perinatal period. Learning from the experiences of other low income countries in handling similar conditions, and considering the nurse-midwives’ views, we developed an innovative approach, called the Four Pillars Approach to antenatal care.

Our primary objective is to evaluate the effectiveness of the Four Pillars Approach in managing pregnant women with anaemia, indicated by a difference in haemoglobin level in pregnancy, improving the frequency of antenatal care attendance and skilled birth attendance during labour. In addition, the secondary objective of this study is to explore the barriers and the facilitating factors of the implementation of the Four Pillars Approach and to evaluate the patient’s and nurse-midwives’ satisfaction with the Four Pillars Approach.

The Four Pillars Approach will be implemented by the trained nurse-midwives in the Public Health Centres in Yogyakarta Special Province. It is expected that this approach will be effective in managing anaemia in pregnancy in order to prevent perinatal morbidity and mortality. If the Four Pillars Approach is effective in improving the outcome of pregnant women with anaemia, this approach could be implemented nationwide and be taken into consideration to improve the outcome for other conditions in pregnancy, after further research.

### Ethical approval

The Ethical Committee of the Faculty of Medicine, Universitas Gadjah Mada – Yogyakarta, has assessed and given the ethical approval for this study.
